#### Primary outcome measure

(i)The recurrence rate of cured participants will be assessed by the symptoms of acute uncomplicated lower UTI. The assessment tools of renewed symptoms will also use the three participant self-rating scales (see Additional file 2): CSESUSI; SSST; and OABSS. If the symptoms of cured patients reappeared in the fourth week after the end of medication, it indicates the participant has relapsed.

#### Secondary outcome measures

(ii)The recurrence rate of cured participants will be assessed by urine leukocytes. If the urine leukocyte value of cured patients increased again in the fourth week after the end of medication, it indicates the participant has relapsed.(iii)The recurrence rate of cured participants will be assessed by bacteriological examination. If the urine culture of cured patients indicated that the original urinary tract pathogen is positive again in the fourth week after the end of medication, it indicates the participant has relapsed.

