#### Primary outcome measure

The symptoms of acute uncomplicated lower UTI will be assessed. The assessment tools for symptoms of acute uncomplicated lower UTI are three participant self-rating scales (see Additional file 2): criteria sheet for evaluating the severity of urinary system infection (CSESUSI; mild: total score ≤ 8, moderate: total score 9–15, severe: total score ≥ 16), if the severity of the disease decreases from severe to moderate, or from moderate to mild, the symptoms are improved; symptoms score sheet of TCM (SSST; cure: total score = 0, effective: total score 0–6, invalid: total score ≥ 6); overactive bladder symptom score (OABSS; if the urgent urination score > 2 and total score > 3, OAB will be diagnosed; mild: total score ≤ 5, moderate: total score 6–11, severe: total score ≥ 12). The CSESUSI will use a scoring method to record the changes of symptoms and signs before and after treatment, such as shivering, fever, dysuria, urinal pain, urinary urgency, urinary frequency, lower abdomen distending pain, lumbago, and percussion tenderness over kidney region. The SSST uses a scoring method to record the changes of symptoms, tongue, and pulse in TCM before and after treatment. The OABSS has been found to be reliable and valid and highly responsive to treatment-related fluctuations in overactive bladder symptoms. Repeating the test after an acceptable treatment interval is an effective way to assess the efficacy of a particular drug regimen on OAB symptoms [33, 34]. If the symptoms disappeared after seven days of treatment, it indicates that the patient is cured. If these symptoms partially disappeared after seven days of treatment, it indicates that the treatment is effective but not cured. If there was no obvious remission and the symptoms of infection persisted after seven days of treatment, it indicates that the treatment is invalid.

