#### Secondary outcome measure

(i)The urine leukocytes of 252 participants will be assessed. If the value of urine leukocytes is returned to normal after seven days of treatment, it indicates the patient is cured. If the value of urine leukocytes is reduced but not returned to normal after seven days of treatment, it indicates that the treatment is effective. If the value of urine leukocytes is still higher than the normal value after seven days, it indicates the treatment is invalid.(ii)The bacteriological examination of 252 participants will be assessed. If the original infected part of the specimen did not regenerate the original infected pathogen after seven days of treatment, it indicates the original bacteria is cleared. If the original pathogen was still cultured in the culture of the specimen from the original infection position, it indicates the original bacteria is not cleared.

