#### Criteria of comprehensive efficacy

(i)Criteria of cure: the evaluation of clinical symptoms reached the level of cure after seven days of treatment; the value of urine leukocytes returned to the normal value; the original infected bacteria was cleared after seven days of treatment. All three criteria must be met.(ii)Criteria of effective treatment: the clinical symptoms were alleviated but did not reach the level of cure after seven days of treatment; the value of urine leukocytes was reduced but not returned to normal after seven days of treatment. Either of these criteria must be met.(iii)Criteria of invalid treatment: the clinical symptoms were not alleviated after seven days of treatment; the value of urine leukocytes was still higher than normal after seven days of treatment; the original infected bacteria were still cultured from the original infection position after seven days of treatment. All three criteria must be met.

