### Recurrence rate

Patients who were cured will attend the second follow-up after 28 days to assess the recurrence rate. Recurrence criteria must include item (i) and either (ii) or (iii) at the same time, or item (i) alone.

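### Leukocyte relapse is defined as a bare increase, without the normal limit that defines leukocyte cure, so the rule read literally counts rises within normal as relapse in a secondary outcome

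*Protocol article*

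**What the plan says.** All references are to the protocol article.

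- **Day 7, leukocytes** (Effective rate, Secondary outcome measure, item i). There are three grades. Cure: "If the value of urine leukocytes is returned to normal after seven days of treatment, it indicates the patient is cured". The effective grade covers a count that has fallen without reaching normal. The third grade, treatment failure, reads: "If the value of urine leukocytes is still higher than the normal value after seven days, it indicates the treatment is invalid".
- **Day 7, comprehensive cure** (Criteria of comprehensive efficacy). The laboratory components are: "the value of urine leukocytes returned to the normal value; the original infected bacteria was cleared after seven days of treatment". Symptom cure is required as well.
- **Day 7, symptom cure** (Effective rate, Primary outcome measure): "If the symptoms disappeared after seven days of treatment, it indicates that the patient is cured". Leukocytes play no part in this definition.
- **Follow-up, leukocytes** (Recurrence rate, Secondary outcome measures, item ii). The measure is introduced as a rate of its own: "The recurrence rate of cured participants will be assessed by urine leukocytes". For that rate, the article then lays down this rule: "If the urine leukocyte value of cured patients increased again in the fourth week after the end of medication, it indicates the participant has relapsed".
- **Overall recurrence** (Recurrence rate): "Recurrence criteria must include item (i) and either (ii) or (iii) at the same time, or item (i) alone". Item (i) is the return of symptoms.

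**The concern.** The same marker is judged on two scales. At day 7 the yardstick for cure is the normal value. At follow-up it is a direction of change, with no limit, no minimum rise and no stated starting value. Two kinds of patient can then be counted as relapsed without having moved from normal to abnormal:

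1. a cured patient whose follow-up count is higher than at day 7 but still normal;
2. a patient cured by symptoms only, whose leukocytes were still above normal at day 7 and rise further. The abnormality never went away, so nothing has recurred.

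At stake is the leukocyte-based recurrence rate. Whether the tablets reduce recurrence is one of the trial's stated questions, and this rate is one of the secondary measures bearing on it. If false relapses occur at a similar rate in all arms, they add noise and shrink any true difference in this measure. Six hospitals will apply the rule, and some could read it as any rise while others read it as above normal.

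**Working it through.** **Step 1. Compare the definitions.**

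| Rule | Yardstick for leukocytes |
|---|---|
| Leukocyte cure, day 7 | normal value |
| Leukocyte effective, day 7 | reduced, and still not normal |
| Leukocyte invalid, day 7 | above the normal value |
| Comprehensive cure, day 7 | normal value |
| Leukocyte relapse, follow-up | increased; no limit named |

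The day-7 grades name the normal value whenever it is meant and use a separate word for direction. The relapse rule has only the word for direction.

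**Step 2. Trace who is affected under each meaning of cured.** The recurrence section does not say which cure applies.

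- Symptom cure: cases 1 and 2 can both arise.
- Leukocyte cure or comprehensive cure: every patient is normal at day 7, so case 2 cannot arise. Case 1 remains.

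**Step 3. Trace which outcomes are affected.** The overall rule is met by item (i) with (ii) or (iii), or by item (i) alone. Item (i) stands in both branches, so it is necessary; the second branch makes it sufficient. The rule reduces to item (i), and a leukocyte rise cannot create or remove an overall recurrence. Only the standalone leukocyte rate can change.

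**Step 4. Illustrate the size of case 1.** The plan gives no figure to reproduce, and all inputs here are assumptions. Take a stable patient with two readings from the same distribution, both within normal. Then

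P(second > first) = (1 − P(tie)) / 2.

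For whole counts I take the two readings as independent, so P(tie) is the sum of the squared probabilities.

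| Assumed distribution within normal | P(any rise) |
|---|---|
| Poisson mean 0.5, truncated to 0–5 | 0.267 |
| Poisson mean 1, truncated to 0–5 | 0.346 |
| Poisson mean 2, truncated to 0–5 | 0.393 |
| Poisson mean 3, truncated to 0–5 | 0.403 |
| Poisson mean 3, truncated to 0–10 | 0.417 |
| Uniform on 0–5: (1 − 1/6)/2 | 0.417 |
| Uniform on 0–10: (1 − 1/11)/2 | 0.455 |
| Continuous, no ties | 0.500 |

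The range is about 27% to 50%. Correlation within a patient that produces more ties would lower the values for counts. If relapse required a value above normal, the figure would be 0% by definition.

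**Step 5. Illustrate the dilution.** With true relapse rate p and the same false-positive rate f in each arm, the observed rate is p + (1 − p)f. A true difference d therefore becomes d(1 − f). Assume true rates of 10% and 20%:

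| f | Observed, p = 0.10 | Observed, p = 0.20 | Difference |
|---|---|---|---|
| 0.27 | 0.10 + 0.90 × 0.27 = 0.343 | 0.20 + 0.80 × 0.27 = 0.416 | 0.073 |
| 0.39 | 0.10 + 0.90 × 0.39 = 0.451 | 0.20 + 0.80 × 0.39 = 0.512 | 0.061 |
| 0.50 | 0.10 + 0.90 × 0.50 = 0.550 | 0.20 + 0.80 × 0.50 = 0.600 | 0.050 |

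The assumed 10-point difference shrinks to about 5 to 7 points.

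**The case against.** The best defence is that the rule concerns cured patients and uses the word *again*, which suggests a return to an earlier raised state. The neighbouring rules have that form: symptoms reappear, or the pathogen is positive again. On this reading the rule already means above normal again, and within-normal rises are never counted. The careful wording at day 7 is also not proof of strict usage, because a value that is reduced but not normal fits both the effective and the invalid grade. This stands in part. The reading is plausible and may be what was intended, but it is not written, and the rule is stated as the operative definition.

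A second defence is that the article is condensed and numerical laboratory limits belong in the full protocol. That is fair for the number itself, whose absence is not criticised here. The point is that the stated relapse rule makes no reference to the normal value, whereas the stated cure rule does.

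A reader might go further and infer that recurrence in this trial is unreliable, or that a real difference in recurrence would be hidden. The documents do not support that: under the Recurrence rate section symptoms decide overall recurrence, and the primary recurrence measure is symptoms. A reader might also infer that the leukocyte rate would consist largely of false relapses. That would need every site to apply the literal reading, and it would rest on distributions and true relapse rates that the documents do not give. Finally, case 2 disappears if cured means comprehensive cure.

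**Conclusion.** The point holds as a defect in the definition of one secondary outcome. The leukocyte relapse rule omits the normal limit that defines leukocyte cure. Taken literally, it counts rises within normal as relapse and, under symptom cure only, further rises in patients who never normalised. That conclusion rests on the text alone.

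The size is illustrative. About a quarter to a half of stable, still-normal patients would be misclassified under the literal reading and the assumed distributions, with independent readings for the count models. The figure is none under the reading that the authors may have intended. The dilution further assumes a false-positive rate that is equal across arms. Overall recurrence and the primary symptom-based recurrence measure are unaffected.

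**What to change.** In Recurrence rate, Secondary outcome measures, item (ii), define leukocyte relapse as a follow-up value above the same upper limit of normal that is used for leukocyte cure at day 7. Count it only in patients whose day-7 value was normal. Report patients still above normal at day 7 separately as persistent, not relapsed, with their number by arm.

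This changes one or two sentences and needs no new visits, tests or data, since urine leukocytes are already assessed at both times. If cured is taken to mean symptom cure, the denominator of this secondary rate will be somewhat smaller than the number followed up, and the report should show both.

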### Safety assessments

Safety measurements included laboratory indices and AEs. All patients will undergo the following laboratory examination before enrollment and at the end of the clinical trial. Changes in laboratory indices before and after the clinical trial will be compared to conducting a safety analysis. Laboratory indices are: (i) routine blood and urine testing; (ii) liver function (AST, ALT, TBIL, DBIL, γ-GT, ALP) and kidney function (Scr, BUN); and (iii) ECG. The occurrence of any AEs in trial participants, such as subjective discomfort of patients and abnormal laboratory results, will be recorded in the CRF during the whole trial process. We will withdraw patients who have severe AEs, as it will be unsafe for them to continue the trial. Meanwhile, we will give them relevant medical care and follow them up until the reaction has terminated.

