**Methods/design:**

In this study, a randomized, double-blind, double-dummy, parallel control of positive drug, multicenter clinical study will be established. A total of 252 patients with acute uncomplicated lower UTI (syndrome of dampness-heat in the lower jiao) will be randomly allocated in the ratio of 1:1:1 to three groups: experimental group; control group 1; and control group 2. The experimental group receives Sanjin tablets plus levofloxacin tablets (LT) placebo; the control group 1 receives LT plus SJT placebo; and the control group 2 receives SJT plus LT on the first five days, SJT plus LT placebo on the last two days. Each group will be treated for seven days and followed-up 1–2 times. The primary outcome measures of effective rate and recurrence rate are symptoms. Secondary outcome measures of effective rate and recurrence rate are the urine leukocytes, bacteriology examination, and safety assessment. Outcomes will be assessed at baseline and after treatment.

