## Method/design

### Objective and design

This is a randomized, double-blind, double-dummy, parallel control of positive drug, multicentre clinical study. The study will be conducted at: the XiYuan Hospital, China Academy of Chinese Medical Sciences; the Longhua Hospital Shanghai University of Traditional Chinese Medicine; the Guangdong Provincial Hospital of Traditional Chinese Medicine; the Hubei Hospital of Traditional Chinese Medicine; the Affiliated hospital of Chengdu University of Traditional Chinese Medicine; and the Yunnan Provincial Hospital of Traditional Chinese Medicine. Ethical clearance for the trial was obtained from ethics committee of the six hospitals. Patients with acute uncomplicated lower UTI will undergo a standardized baseline evaluation before treatment, comprising detailed history taking, physical examination, and laboratory testing. All included patients are randomly divided into three groups: experimental group; control group 1; and control group 2. The experimental group receives SJT plus levofloxacin tablets (LT) placebo; control group 1 receives LT plus SJT placebo; and control group 2 receives SJT plus LT on the first five days, SJT plus LT placebo on the last two days. After seven days of treatment, the efficacy and safety of three groups will be evaluated. The first aim is to determine whether SJT can reduce the use of antibiotics (control group 2 versus control group 1, non-inferiority test); the second aim is to determine whether SJT can substitute the use of antibiotics (experimental group versus control group 1, non-inferiority test). The recurrence rate will be assessed at the 28-day follow-up after being cured to determine whether SJT can reduce the recurrence rate. The trial is conducted in accordance with the World Medical Association Declaration of Helsinki and Good Clinical Practice of Pharmaceutical Products [17, 18]. After a full explanation by the clinicians, written informed consent will be obtained from the participants before intervention [19, 20]. Strict data management and quality control will be conducted in this trial [21, 22]. This trial was registered in the Clinical Trials USA registry (registration No. NCT03658291) on 4 September 2018 and will be carried out from January 2019 to December 2019. The study design is shown in Fig. 1. The protocol follows the recommendations of the SPIRIT initiative (see Additional file 1) [23] and the trial results will be reported according to the latest version of the CONSORT statement [24].

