## Follow-up

All included patients will be re-evaluated after seven days of treatment follow-ups as an outpatient to assess the efficacy and safety. The patients who were cured will receive the second follow-up after 28 days to assess the recurrence rate. Patients whose symptoms worsened will receive a supply of relevant medicine and a written withdrawal schedule. Assessment of study endpoints and duration of follow-up is shown in Fig. 2.

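### Adverse events (AEs) are recorded with no common end day and only cured patients return about 28 days later, so a crude AE comparison can rest on windows set by treatment success

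*Protocol article*

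**What the plan says.** All places are in the protocol article.

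- **Visits.** The abstract's Methods/design paragraph says: "Each group will be treated for seven days and followed-up 1–2 times". Under Follow-up, the first visit is for everyone: "All included patients will be re-evaluated after seven days of treatment follow-ups as an outpatient to assess the efficacy and safety". The second depends on outcome: "The patients who were cured will receive the second follow-up after 28 days to assess the recurrence rate". The primary outcome under Recurrence rate dates that assessment: "If the symptoms of cured patients reappeared in the fourth week after the end of medication, it indicates the participant has relapsed".
- **Time of the safety evaluation.** Objective and design says: "After seven days of treatment, the efficacy and safety of three groups will be evaluated". The abstract lists safety among the secondary outcomes and has outcomes assessed at baseline and after treatment.
- **Safety assessments.** On laboratory tests and ECG: "All patients will undergo the following laboratory examination before enrollment and at the end of the clinical trial". AEs, including patients' discomfort and abnormal laboratory results, "will be recorded in the CRF during the whole trial process". For patients with severe AEs, who are withdrawn, the clinicians will "follow them up until the reaction has terminated".
- **Data analysis.** The safety dataset is defined by having taken a study drug at least once and having post-treatment safety data, with no time window. Counted indices are compared by the chi-squared test, two-sided, at 0.05.

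**The concern.** The length of a patient's time in the trial depends on whether that patient was cured. Cure is an efficacy result that arises after randomisation and may differ between arms, particularly as the experimental group receives no active antibiotic. If AEs are counted over each patient's own time in the trial, randomisation no longer protects the comparison: two arms with identical AE risk, on and off drug, can show different AE proportions because one was watched for longer.

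Safety is a stated aim of the trial, and the Discussion part of the abstract promises reliable safety evidence for clinical treatment. A shift of a few points between arms would bear on that conclusion. An analysis plan could later cut the AE count at day 7, but the protocol text gives no such rule and, as written, points to the longer count.

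**Working it through.** **The plan's own figure.** The document gives no AE rate, cure rate or safety power, so there is nothing to reproduce. The timeline can be rebuilt and the effect of unequal windows illustrated.

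**Timeline**
- Treatment: 7 days (Interventions).
- Second visit, cured patients only: 28 days later, in the fourth week after the end of medication. So 7 + 28 = day 35.
- Literal AE window: about 7 days if not cured and about 35 days if cured, a ratio of 5.

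**Mean observation per patient** at cure rate c is 7(1 − c) + 35c:
- c = 0.5: 3.5 + 17.5 = 21.0 days
- c = 0.7: 2.1 + 24.5 = 26.6 days

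**Artificial difference in AE proportions**

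Assumptions, none of them from the document: a 10% risk of at least one AE over the seven treatment days; a constant daily hazard L on drug and rL off drug, the same in both arms; cure rates of 50% and 70%; every patient observed for at least the seven days. From the document: 252 patients at 1:1:1, so 84 per arm.

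L = −ln(0.9)/7 = 0.01505 per day.

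P(at least one AE) = (1 − c)(1 − exp(−7L)) + c(1 − exp(−L(7 + 28r)))

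Since exp(−7L) = 0.9, the second bracket is 1 − 0.9^(1 + 4r). The difference between arms reduces to (0.7 − 0.5) × (0.9 − 0.9^(1 + 4r)).

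Worked case, r = 1: 0.9^5 = 0.5905, so a cured patient's risk over 35 days is 0.4095.
- c = 0.5: 0.5 × 0.1 + 0.5 × 0.4095 = 0.255
- c = 0.7: 0.3 × 0.1 + 0.7 × 0.4095 = 0.317
- Difference: 0.062

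The last column is the chance that a two-sided 0.05 comparison of two proportions, 84 per arm, gives a nominally significant excess in the arm that cures more. The reference for one tail is 2.5%.

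| Off/on-drug hazard ratio r | AE proportion, cure 50% | AE proportion, cure 70% | Artificial excess (points) | Chance of significant excess |
|---|---|---|---|---|
| 0 | 10.0% | 10.0% | 0.0 | 2.5% (reference) |
| 0.1 | 11.9% | 12.6% | 0.7 | 3.5% |
| 0.25 | 14.5% | 16.3% | 1.8 | 5.1% |
| 0.5 | 18.5% | 22.0% | 3.4 | 7.9% |
| 1 | 25.5% | 31.7% | 6.2 | 14.1% |

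**Sensitivity.** With cure rates of 40% and 80% and r = 1, the excess is 12.4 points and the chance 42.6%. Across seven-day AE risks of 5% to 20% and cure pairs 50/60, 50/70 and 40/80, the excess runs from 0 to 18.9 points. The top of that range needs the highest AE risk, the widest cure gap and equal hazards on and off drug all at once.

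**With a common cut-off at the day-7 visit**, days 8 to 35 do not count. This is the r = 0 row: the artificial difference is 0.0 points at any pair of cure rates.

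**Laboratory tests and ECG.** No arithmetic applies. The abstract, Objective and design, and Follow-up all place the safety evaluation after seven days of treatment. The recurrence sections attach only symptoms, urine leukocytes and culture to the later visit. Safety assessments alone uses an undated end-of-trial phrase, and applies it to all patients. The only scheduled post-treatment visit that includes all patients is the seven-day one.

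**The case against.** The strongest reply is that the document already puts the safety evaluation at seven days for everyone and gives the second visit one purpose, recurrence. The assessment schedule is in Fig. 2, which is not reproduced in the text available here, and the article condenses a fuller protocol. Visit-level timing may be settled in either.

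For laboratory tests and ECG this reply largely stands. A reader might infer that cured patients have closing tests about 28 days off drug and uncured patients at day 7. The document does not support that: an undated phrase is set against several sections that point to day 7.

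Three further limits also stand.
- A reader might infer that the arm that cures more will look less safe. That needs arms that differ in cure rate and AEs that arise after treatment. Were closing tests in fact drawn late, transient on-drug changes could have resolved, and that arm could look safer on laboratory and ECG results.
- A reader might infer that observation stops at day 7 in every uncured patient. Severe AEs are followed to their end whatever the cure status, and under Exit criteria patients who do not improve may leave before day 7.
- Applying the on-drug hazard unchanged to the 28 off-drug days is a high-end choice. At hazard ratios of 0.1 to 0.25, the illustration gives only 0.7 to 1.8 points.

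The reply does not dispose of the AE window. That wording extends recording over the whole trial, the length of the trial depends on cure, and the safety dataset carries no window.

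**Conclusion.** The point holds for AE recording. Followed as written, AE capture is about five times as long in cured as in uncured patients, apart from the follow-up of severe AEs. A crude chi-squared comparison of AE proportions can then favour the arm that cures fewer patients when true risk is equal.

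The size is conditional. At a 10% seven-day AE risk and cure rates of 50% and 70%, the artificial excess is 0 points with no off-drug AEs, 0.7 to 3.4 points at hazard ratios of 0.1 to 0.5, and 6.2 points at equal hazards. The AE risk, cure rates and hazard ratio are all assumed, as is the use of the general chi-squared rule for AE proportions. Larger gaps can be produced only by combining wider cure differences with high off-drug risk, for which the document gives no support.

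For laboratory tests and ECG the finding is limited to an undefined time point that must be reconciled with the sections placing the safety evaluation after seven days. It is not shown that those results are collected over cure-dependent windows.

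**What to change.** 1. Under Safety assessments and Data analysis, make AEs from first dose to the day-7 visit, or to early withdrawal, the between-arm safety comparison.
2. Report AEs after day 7 in cured patients separately, or per person-time, and label them as coming from a group selected by outcome.
3. Replace the undated end-of-trial phrase with a statement that closing laboratory tests and ECG are done at the day-7 visit in every patient, in line with the abstract, Objective and design, and Follow-up. Check that Fig. 2 agrees.

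The cost is protocol wording, with no extra patients, visits or tests. The downside is that later AEs drop out of the main comparison. A telephone contact at about day 35 for uncured patients would make the later AEs comparable too, but it is optional: the day-7 cut-off alone removes the artificial difference.
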